Can participation in the team sports and individual sports conditions be explained by the constructs of the Sport Commitment Model?We hypothesize that participation will be predicted by sports commitment as per the tenets of the Sport Commitment Model. Commitment will be predicted primarily by enjoyment (+), social constraints from family obligations/involvement alternatives (−), and social involvement opportunities/personal investments (+).Can group differences among these motivational and behavioral outcomes be explained through a mediation model?We propose that the covariance of the assigned conditions on psychosocial outcomes will be explained by sport participation. In turn, the covariance between participation and assigned conditions will be explained by salient underlying motives from the Sport Commitment Model. In particular, enjoyment will explain the differences between both sport conditions, but the better psychosocial outcomes from team sports will be explained by the additional involvement opportunities of friendship and social interaction.Is there a seasonal, gender, dual/single parent, age of child, or type of sport difference across primary outcomes by assigned condition?Differences in season, gender, age of child, and type of sport are exploratory research questions. It is possible that both sport conditions may have participation lowered by weather conditions in the winter. Men may participate in sport more due to lower childrearing expectations; however, there is currently limited research to support this conjecture. Similarly, younger children may impact sport participation because of the considerable care needs of young children. Finally, it is possible types of sport could differ in their psychosocial outcomes for reasons such as the structure or environment of participation.

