### Analysis strategy

Missing data will be inspected to determine the appropriate imputation procedures [43], and normality of all variables will be checked to determine whether any transformations are required. To determine whether psychosocial outcomes change over time similarly for all three conditions (i.e., to address objective 1), a level 1 model will be specified wherein the intercept (i.e., value of the outcome at baseline) will be allowed to vary randomly (i.e., vary across participants) and the slope for the linear trend will be constrained to be fixed (i.e., the same across participants), controlling for any significant covariates at level 2. Additionally, dummy variables will be created for condition (team sports: 1 = yes or 2 = no; individual sport: 1 = yes or 2 = no; control: 1 = yes or 2 = no) at level 2, with the team sport and individual sport variables being added to the model to predict the intercept and slope at level 1. In doing so, the control group is compared with the other two groups to determine if baseline psychosocial outcomes are similar across conditions and whether the change is similar across conditions. Follow-up analyses will be conducted for the group comparison. To determine whether participation within the team and individual sport conditions is explained by the Sport Commitment Model constructs (i.e., secondary objective 1), a time-varying covariate analysis will be used. For example, within the team sport condition, participation will be predicted by a level 1 model that includes a random intercept, fixed slope, and the time-varying Sport Commitment Model constructs. The same will then be done for the individual sport condition. To determine whether the change in the underlying motives explains the potential change in sport participation during the intervention similarly for all three groups (i.e., to address secondary objective 2), a time-varying covariate mediation analysis approach will be used following the procedure outlined by Krull and MacKinnon [44] for level 1 mediation. Briefly, the analyses needed to establish mediation will treat the underlying motives as time-varying covariates at level 1 of the model. Then, the dummy-coded condition variables will be entered at level 2 to determine if the mediation relationships are similar across groups. Finally, to determine whether there is a seasonal, gender, or sport type (within team or individual) difference across the primary and secondary outcomes (i.e., to address secondary objective 3), each variable will be entered into the various models at level 2 to predict the intercepts and slopes at level 1. Doing so will determine if they impact the change in the various outcomes across time.

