### Intervention description, schedule, procedures, and protocol

After interested participants are deemed eligible and enrolled, they are booked for a baseline meeting. At this meeting, informed consent is obtained by a research assistant, then participants are asked to complete a baseline questionnaire containing demographic, sports commitment/behavior, and quality of life items (*see* Fig. 1 for enrollment schedule). Next, participants are randomized to one of three conditions. A research assistant who is blind to each participant’s condition presents the participant with a prepackaged envelope that reveals the condition allocation. The research assistant then outlines possible activity options and provides resources to facilitate registration in an activity program when required. Condition allocation will not require alteration of usual care pathways (including use of any medication), and these will continue for all trial arms.

Participants in the control condition are asked to use the honorarium funds to treat themselves to a weekly “night out” or “personal time” of their choice, as long as the time is not physically active and the time is spent away from their children. Examples of personal time are provided, such as going for coffee, going to the movies, or taking a workshop or class. Participants in the personal time control condition are told they will not receive any further contact until the next assessment period.

Participants in the team sport choice condition are asked to make a selection from a customized and up-to-date handout of the environmental scan of the available adult team sport programs in Greater Victoria. Participants in the team sport condition are instructed that their team sport choice must follow the basic definition set forth by Eime and colleagues [27], in which at least two participants are active in a necessary collaboration to achieve the objective of the physical activity within a set of rules. These include but are not limited to basketball, soccer, volleyball, dragon boating, and so forth. However, due to the limited nature of team sport seasons, options were somewhat constrained, depending on the time of year. Therefore, to assist with retention and autonomy in terms of choice, the criteria for team sport was slightly adapted and expanded to include registered programs that meet weekly with the same group, such as kickboxing classes, running groups, and bootcamps.

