Finally, participants in the individual sport choice condition are provided with a customized handout of our environmental scan of available adult individual sports programs in Greater Victoria (maintained and updated) and asked to choose one of these available options. “Individual sport” is defined as a physical activity performed or completed by an individual with a structured rule set of competition or progression toward an outcome or goal. Individual sports include rowing, running, cycling, swimming, and rock climbing.

Upon allocation, participants are asked to begin their activity as soon as possible (i.e., register for a team sport, choose an individual sport or “personal time” activity, and commence weekly sessions). Participants in both sport conditions are asked to keep track of their attendance in the program. After the initial 6 weeks, participants are sent follow-up questionnaires to complete via email. Contact is made initially with a phone call by the research assistant to answer any questions the participants may have about their experiences over the last 6 weeks. A phone-assisted report of sport participation over the past 6 weeks is also ascertained at this time. A similar protocol is followed at the 3-month mark; however, participants are asked to come to the laboratory to partake in a brief wrap-up interview and an end-of-trial questionnaire (*see* Fig. 1 for schedule of interventions and assessments). To assist study retention, we offer to subsidize the program chosen by participants with a maximum $80 contribution toward registration (or the personal time activity of choice for the control participants) as well as a maximum $25-per-week contribution toward childcare when needed. Participants must complete the study in order to receive the honorarium.

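### In an exploratory analysis, sport type is chosen by parents after allocation and, in the team arm, tied to season, yet it is modelled like gender and season and read as an impact on change.

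*Protocol article*

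**What the plan says.** The third secondary question, in the protocol article under Present research aims and hypotheses, asks about a "seasonal, gender, dual/single parent, age of child, or type of sport difference across primary outcomes by assigned condition". The same section calls season, gender, age of child and type of sport exploratory, and suggests it is possible that "types of sport could differ in their psychosocial outcomes for reasons such as the structure or environment of participation".

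Under Analysis strategy, the analysis assigned to this question is "to determine whether there is a seasonal, gender, or sport type (within team or individual) difference across the primary and secondary outcomes". Each variable is to predict the level 1 intercepts and slopes from level 2, and the article concludes: "Doing so will determine if they impact the change in the various outcomes across time".

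The order of events is given under Intervention description, schedule, procedures, and protocol. The baseline questionnaire comes first. "Next, participants are randomized to one of three conditions". Only then do parents pick an activity: "Participants in the team sport choice condition are asked to make a selection from a customized and up-to-date handout", with a similar handout for the individual arm, and after allocation they are asked to "register for a team sport, choose an individual sport or" a personal-time activity. For the team arm the section adds that "due to the limited nature of team sport seasons, options were somewhat constrained, depending on the time of year", and that the arm was widened to other weekly group programmes for this reason.

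**The concern.** Gender and enrolment season do not depend on anything a parent decides after allocation. Sport type does. Parents who pick one sport over another may differ in fitness, sociability, free time or childcare, and any of these may also affect how their scores change. In the team arm the calendar also shapes the choice, because enrolment runs in waves aligned with sport seasons (Recruitment procedure) and the options vary with the time of year. A slope that differs by sport type is therefore a non-randomised contrast, and impact is a causal word for it.

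What is at stake is limited. A seasonal or self-selected difference could be credited to a sport's structure or environment, which is the explanation the aims already offer. The second issue is one of coverage: two of the five factors in the question have no analysis in the section meant to answer it.

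**Working it through.** The article gives no figure for this analysis, so there is none to reproduce. The first two checks are documentary. The third is an illustration on stated assumptions.

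**1. Status of each variable.**
- Gender: fixed before randomisation.
- Season: set by the enrolment wave, so known before randomisation.
- Sport type: chosen by the parent after randomisation, in both sport arms.
- Seasonal limit on choice: stated for team sport only. In the individual arm only self-selection is at issue.
- Intercept: the article defines it as the baseline value, which is measured before the sport is chosen. A sport-type term on the intercept can show how choosers differed at the start. It does not remove confounding of the slope.

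**2. Coverage of the question.**
- Aims, five factors: season, gender, dual/single parent, age of child, type of sport.
- Analysis strategy, three factors: season, gender, sport type.
- Without an analysis: dual/single parent and age of child. The Demographics section collects marital status and children's ages.

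**3. Illustration of the seasonal part (team arm).**

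From the documents: 240 enrolled less 25% attrition is 180, or 60 per arm. Assumed: half enrol off-season; 60 to 80% of off-season parents and 20% of in-season parents take a class-type programme; season alone shifts 3-month change by 0.3 or 0.4 SD; the true sport effect is zero; the SD of change is 1.

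False difference = (off-season share among class users − off-season share among the rest) × season effect. The rejection rate is the two-sided 5% normal test with SE = √(1/n₁ + 1/n₂).

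- *60% versus 20% uptake.* The shares are 0.30/(0.30 + 0.10) = 0.75 and 0.20/(0.20 + 0.40) = 0.33, a gap of 0.42. Groups are 24 and 36, SE 0.264. A season effect of 0.3 SD gives 0.125 SD and 7.6% rejections; 0.4 SD gives 0.167 SD and 9.7%.
- *80% versus 20% uptake.* The gap is 0.80 − 0.20 = 0.60. Groups are 30 and 30, SE 0.258. A season effect of 0.3 SD gives 0.18 SD and 10.7%; 0.4 SD gives 0.24 SD and 15.3%.

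A simulation with 69 in one arm (207/3), 4,000 runs, least squares on change and a season effect of 0.4 SD gave the results below. The 70/30 and 80/20 labels are the shares taking one sport type in the two seasons. Self-selection is an assumed trait worth 0.3 SD of change per SD, with an odds ratio of 2 per SD for choosing one sport type; the self-selection-only row has no season effect.

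| Scenario (true sport effect zero) | Sport type alone | Sport type and season together |
|---|---|---|
| No season-sport link | 0.01 SD, 5% | 0.01 SD, 5% |
| 70/30 link | 0.16 SD, 10% | 0.00 SD, about 5% |
| 80/20 link | 0.24 SD, 16% | about 0.00 SD, about 5% |
| 80/20 link plus self-selection | 0.35 SD, 30% | 0.19 SD, 10% |
| Self-selection only | 0.19 SD, 12% | 0.19 SD, 11% |

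Entering season jointly removes the seasonal part. It does nothing for self-selection.

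**The case against.** The strongest reply is that the article already contains most of the safeguards. The aims label type of sport exploratory and say only that differences are possible. The analysis is already restricted to comparisons within the team or individual arm. Season is itself a planned level 2 predictor, and whether it shares a model with sport type is a detail an article may leave to a fuller document. The Pilot research section reports that the sports parents preferred run in every season, and the limit reported later is described as only partial. On winter, the aims raise a possible drop in participation; they do not state an expected shift in psychosocial change. The season effects used above have no source in the text.

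Most of this stands, and it limits the point in four ways:
- A reader might infer that sport type is undefined for controls and so breaks the analysis. It does not, because the planned comparison stays within each sport arm.
- A reader might infer that variables are certainly entered one at a time. The wording can be read that way but does not say so.
- A reader might infer that season distorts the sport-type comparison in both arms. The limit is stated for team sport only, and the Pilot research statement needs to be reconciled with it.
- A reader might infer that a seasonal or self-selected difference will be reported as a sport effect. The text makes that possible, not certain.

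What the reply does not answer is the wording. Exploratory status does not turn a self-selected, post-allocation variable into one whose coefficient shows impact, and joint entry of season would still leave self-selection. Nor does it explain why the list stops at three of five factors.

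**Conclusion.** The point holds as a minor one. Sport type is chosen by participants after allocation and, in the team arm, is partly governed by the time of year. Its slope can describe an association but cannot determine an impact. The randomised comparison of the three conditions is unaffected.

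No size can be given from the documents. The 8 to 15% false-positive range rests wholly on the assumed season effect, uptake pattern and off-season split; with no link between season and sport the rate is the nominal 5%. The range is not an estimate of what this trial will show. The self-selection figures are likewise assumed.

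The three-against-five mismatch needs no assumption. It is an incomplete list rather than a loss of data, since the relevant characteristics are collected.

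**What to change.** Keep the within-arm analysis of sport type and make three wording changes under Analysis strategy:

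1. State that sport type is chosen after allocation, and that its model also contains season or wave, baseline score, gender and child age, entered together.
2. For sport type, replace the claim to determine impact with wording such as *describe whether change differs by sport type*, reported as a non-randomised association.
3. Add dual/single parent status and age of child to the list, so that it covers all five factors in the third secondary question.

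Also reconcile the Pilot research statement on year-round availability with the later account of constrained team options.

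The cost is analysis wording only. Season follows from the enrolment wave, and the other characteristics are already collected (dual/single status would be derived from marital status). There are two downsides. No causal statement about sport type will be possible. The sport-type term also loses some precision: under the illustrative links its standard error rises by a factor of √(1/(1 − 0.4²)) = 1.09 at 70/30, or √(1/(1 − 0.6²)) = 1.25 at 80/20, from adding season alone.

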### Randomization, allocation, and blinding

Randomization is performed by the project coordinator using Excel Sheet Randomization at a 1:1:1 allocation ratio. A research assistant then prepackages envelopes containing certificates that indicate condition assignment along with a list of potential ideas and resources for that condition. A second research assistant who is blind to participants’ condition presents the participants with their randomized allocation.

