
### Justification of sample size

Given the hierarchical nature of the data (i.e., the three measurement occasions at level 1 were considered to be nested within the participant at level 2), the optimal design program for power estimation of hierarchical linear models [45] was used. With three measurement occasions, three groups, and a small to moderate effect size (0.40), a total of 207 participants (i.e., 67 parents per condition) were needed to show significant differences over time. Inclusive of a potential 25% attrition rate, the total sample size required is 240.

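### The moderator model for secondary question 3 has no moderator-by-condition term, so it cannot show whether condition effects differ by season, gender, parent status or age of child

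*Protocol article*

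**What the plan says.** Under Present research aims and hypotheses, the third secondary question reads: "Is there a seasonal, gender, dual/single parent, age of child, or type of sport difference across primary outcomes by assigned condition". The text after it classes most of these as exploratory: "Differences in season, gender, age of child, and type of sport are exploratory research questions". Dual/single parent status is not in that sentence.

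The Analysis strategy restates the objective as "to determine whether there is a seasonal, gender, or sport type (within team or individual) difference across the primary and secondary outcomes". Its method is "each variable will be entered into the various models at level 2 to predict the intercepts and slopes at level 1", and its stated yield is "Doing so will determine if they impact the change in the various outcomes across time".

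In the outcome model for objective 1, condition is handled by dummy variables at level 2, "with the team sport and individual sport variables being added to the model to predict the intercept and slope at level 1".

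**The concern.** The question is one of effect modification: does the benefit of team or individual sport over personal time depend on season, gender, family structure or the child's age? The model described addresses something else, namely whether outcomes change at a different rate in, say, women than in men, averaged over arms.

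The two can disagree in either direction. A moderator can change the trajectory equally in every arm without altering any condition effect. It can also reverse the condition effects and leave the average trajectory unchanged. Followed as written, the outcome model would leave secondary question 3 unanswered for season and gender. For dual/single parent status and age of child, no analysis is described at all.

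**Working it through.** **1. Question and method side by side**

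| | Aims, secondary question 3 | Analysis strategy, secondary objective 3 |
|---|---|---|
| Moderators | season, gender, dual/single parent, age of child, type of sport | season, gender, sport type (within team or individual) |
| Target | difference by assigned arm | effect on change over time, arm not mentioned |
| Moderator-by-condition term | implied by the question | none described |

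**2. The planned slope equation**

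For a binary moderator M, the text gives: slope = g0 + g1·Team + g2·Indiv + g3·M.

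The team-versus-control effect is g1 whatever the value of M, and the individual-versus-control effect is g2. No parameter lets either vary with M. Answering the question needs two more terms, g4·Team·M + g5·Indiv·M.

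**3. What g3 estimates**

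Let D be the difference in slope between the two moderator levels within an arm. With arms of equal size ("Excel Sheet Randomization at a 1:1:1 allocation ratio") and the same moderator split in each:

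- planned coefficient: g3 = (D_control + D_team + D_indiv) / 3
- terms the question needs: g4 = D_team − D_control, and g5 = D_indiv − D_control

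The effect sizes below are assumptions. Only the value 0.40 appears in the article, as the design effect size in the sample-size section.

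| Scenario | D control, team, indiv | g3 | g4, g5 |
|---|---|---|---|
| Same shift in every arm | 0.40, 0.40, 0.40 | 0.40 | 0, 0 |
| Team effect 0.40 then 0, individual effect 0 then 0.40 | 0, −0.40, +0.40 | 0 | −0.40, +0.40 |
| Team effect 0 then 0.80 | 0, 0.80, 0 | 0.80/3 = 0.27 | 0.80, 0 |

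In the second scenario with an even split, g1 and g2 each come out at (0.40 + 0)/2 = 0.20, which hides the reversal.

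**4. Illustrative rejection rates**

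Assumptions not in the article: residual SD 1 on the change scale, a 50:50 moderator split and two-sided 5% tests. The total of 240 ("Inclusive of a potential 25% attrition rate, the total sample size required is 240") gives 80 per arm. In 4,000 simulated trials:

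- same shift of 0.40 in every arm: the planned term is significant in about 88% and the joint 2-df product test in about 5%
- crossing scenario: the planned term is significant in 4.6% and the product test in about 61%

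Analytic check of the 88%: SE(g3) = 1/√(240 × 0.5 × 0.5) = 0.129 and 0.40/0.129 = 3.10, for power of about 87%.

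Range over SD 0.8 to 1.2, splits of 50:50 and 20:80, and 80 or 60 per arm (240 × 0.75 / 3 = 60), using SE(g3) = SD/√(N·p·(1−p)) and the matching noncentral F for the products:

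- planned term under the common shift: about 43% to 97%
- product test under the crossing scenario: about 23% to 81%

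**5. Precision of the needed terms**

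The SE of a condition effect is SD·√(2/n). The SE of a product term is SD·√(2/(n·p·(1−p))). Their ratio is 1/√(p(1−p)), which is 2 at 50:50 and 2.5 at 20:80. With n = 60 per arm, SD 1 and an even split these are 0.18 and 0.37, so a single product of 0.40 would be detected in about 19% of trials.

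**The case against.** Several points on the other side stand.

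- **Sport type is not part of the problem.** It is nested in arm, since controls have no sport and the two sport arms choose from different lists. A product with condition is not the right term, and the article already confines the comparison to within team or within individual.
- **The exploratory label is mostly there.** The aims section applies it to every moderator except dual/single parent status. Neither the primary comparison nor the sample size rests on this question.
- **Not every model pools the arms.** The models for secondary objective 1 are fitted separately in the team and individual arms, so a moderator entered there is already specific to the arm. The point concerns the objective 1 outcome models, which carry the primary outcomes.
- **The article describes its own output accurately.** A reader might infer that the trial will report a general time trend as a difference in the effect of sport. The documents do not say so; they promise only an effect on change over time. Nor is the 88% a false-positive rate. It is ordinary power for a real moderator-by-time effect, and an error only if read as a difference between arms.

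Two arguments do not remove the mismatch. The first is that the commentary under the question is largely about participation, so that the question may not mean effect modification. Its wording nevertheless asks about primary outcomes by assigned arm. The second is that interaction terms are commonly left to an analysis plan. Here the article does fix a model: it names the level, the parameters predicted and what they will show. Because condition is itself a level 2 predictor, the level 1 slope can only be the time slope, not a condition effect.

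**Conclusion.** The concern holds for season and gender as modelled, and for dual/single parent status and age of child, which the question names and the analysis omits. As described, the outcome model cannot detect a difference in condition effect across moderator levels and cannot rule one out. This follows from the form of the model and needs no numerical assumption.

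The numbers are illustrations only. The SD, the effect sizes and the subgroup split are not in the article. The simple average for g3 relies on equal arms with the same split in each, and the rejection rates move widely over plausible inputs.

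The consequence is moderate: an exploratory question would go unanswered, and the main trial conclusion is unaffected. It should be corrected before the final analysis.

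**What to change.** In the objective 1 outcome models, add moderator-by-condition terms predicting the slope (moderator by condition by time) for season, gender, dual/single parent status and age of child. Test the product terms jointly for each moderator, and report the condition effects at each level with confidence intervals.

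Make the moderator lists in the aims and in the Analysis strategy agree. Keep the exploratory label and extend it to dual/single parent status. Keep sport type as the planned within-arm comparison, and state that participants choose their sport, so that comparison is not randomised.

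The cost is some wording and a few model terms. Gender, marital status and children's ages are already collected at baseline, and season follows from the enrolment wave. The article has recruitment running to December 2021 and analysis through 2022, which leaves room for the change. The drawback is low power: a product term has at least twice the standard error of the matching condition effect. The report should say so, and should not read a non-significant interaction as evidence that effects are equal.
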